# Perineal wound closure using gluteal turnover flap or primary closure after abdominoperineal resection for rectal cancer: study protocol of a randomised controlled multicentre trial (BIOPEX-2 study)

**DOI:** 10.1186/s12893-020-00823-7

**Published:** 2020-07-23

**Keywords:** Abdominoperineal resection, Rectal cancer, Primary perineal wound closure, Gluteal turnover flap, Perineal wound infection and perineal wound healing

## Abstract

**Background:**

Abdominoperineal resection (APR) for rectal cancer is associated with high morbidity of the perineal wound, and controversy exists about the optimal closure technique. Primary perineal wound closure is still the standard of care in the Netherlands. Biological mesh closure did not improve wound healing in our previous randomised controlled trial (BIOPEX-study). It is suggested, based on meta-analysis of cohort studies, that filling of the perineal defect with well-vascularised tissue improves perineal wound healing. A gluteal turnover flap seems to be a promising method for this purpose, and with the advantage of not having a donor site scar. The aim of this study is to investigate whether a gluteal turnover flap improves the uncomplicated perineal wound healing after APR for rectal cancer.

**Methods:**

Patients with primary or recurrent rectal cancer who are planned for APR will be considered eligible in this multicentre randomised controlled trial. Exclusion criteria are total exenteration, sacral resection above S4/S5, intersphincteric APR, biological mesh closure of the pelvic floor, collagen disorders, and severe systemic diseases. A total of 160 patients will be randomised between gluteal turnover flap (experimental arm) and primary closure (control arm). The total follow-up duration is 12 months, and outcome assessors and patients will be blinded for type of perineal wound closure. The primary outcome is the percentage of uncomplicated perineal wound healing on day 30, defined as a Southampton wound score of less than two. Secondary outcomes include time to perineal wound closure, incidence of perineal hernia, the number, duration and nature of the complications, re-interventions, quality of life and urogenital function.

**Discussion:**

The uncomplicated perineal wound healing rate is expected to increase from 65 to 85% by using the gluteal turnover flap. With proven effectiveness, a quick implementation of this relatively simple surgical technique is expected to take place.

**Trial registration:**

The trial was retrospectively registered at Clinicaltrials.gov NCT04004650 on July 2, 2019.

## Background

Historically, abdominoperineal resection (APR) has been the standard treatment for (low) rectal cancer. Although most rectal cancer patients nowadays undergo a restorative total mesorectal excision (TME), an APR is still performed in selected patients with very low tumours and/or poor sphincter function. A drawback of APR is the resulting perineal defect that still poses a high risk of morbidity, especially in patients who have undergone pre-operative (chemo)radiotherapy [1]. Early perineal wound complications occur in up to 35% of patients, and 10% of patients still have a wound complication even 1 year after the operation [2, 3].

The high rate of perineal morbidity after primary wound closure has resulted in a continuous discussion on alternative closure methods for the perineal wound after APR. Options include biological mesh closure and (muscle) flap assisted closure. Biological mesh closure has been investigated in our previous randomised controlled trial (BIOPEX-study), and showed no superiority in perineal wound healing compared to primary closure. Biological mesh closure did result in a lower perineal hernia rate 1 year after APR (13% versus 27%; *P* = 0.0316) [2]. The absence of improvement in perineal wound healing after biological mesh closure is probably related to the formation of a dead space between the mesh and the perineal skin after APR. This dead space is prone to fluid accumulation, which can subsequently get infected with abscess formation.

The hypothesis is that filing of the dead space by well-vascularised soft tissue can prevent fluid accumulation, and thereby reduce infectious complications and abscess formation. Several myocutaneous and fasciocutaneous flaps have been used for this purpose. In a systematic review of cohort studies, muscle flap closure of the perineal wound showed an improvement of 20% compared to primary closure of perineal defects after oncological resection [4]. However, downsides of these flaps are the donor-site and recipient-site morbidity that are both often neglected, besides the complexity of the reconstructive procedures with the need for the presence of a plastic surgeon, and substantially increased operative time. Especially in the case of a rectus abdominis muscle flap, the flap interferes with the benefits of a laparoscopic approach of the APR and gives a high risk of donor site morbidity. Furthermore, there might be an impact on cosmesis due to an additional scar.

A gluteal turnover flap is a small transposition flap consisting of the adjacent skin and subcutaneous tissue of one of the buttocks. This flap is deepithelialised and dissected down to the gluteal muscle, it is perfused through perforating blood vessels from the underlying muscle. The flap is hinged into the resected space of the anal sphincter complex, and the dermis is stitched to the contralateral levator remnant as a pelvic floor closure. The skin is closed in layers over the flap in the midline, thereby not creating an additional scar, and minimizing donor-site morbidity. Moreover, it is a relatively simple procedure, which is easy to learn, and can be performed without the need of a plastic surgeon.

Potentially, the gluteal turnover flap both improves wound healing by filling the dead space, as well as preventing hernia formation by stitching deepithelialised dermis to the levator remnant. A pilot study of this gluteal turnover flap showed no flap necrosis, and no major morbidity requiring radiological or surgical re-intervention within 30 days [5].

The aim of this randomised controlled multicentre trial is to compare the effect of gluteal turnover flap closure of the perineal wound with primary perineal wound closure after APR for rectal cancer with regard to perineal wound healing.

## Methods/design

### Objective

The objective of this study is to investigate the effect of gluteal turnover flap closure of the perineal wound with primary closure of the perineal wound after APR for rectal cancer. The hypothesis is that gluteal turnover flap reconstruction increases the uncomplicated perineal wound healing rate, and decreases the occurrence of perineal hernia.

**Fig. 1 Fig1:**
[figure not shown]
Flow-diagram: study design

Perineal wound healing will be assessed at 14 days, and 1, 3, 6 and 12 months postoperatively using the Southampton wound score (Table 1). Evaluation will be performed by an independent observer not aware of treatment allocation. The perineal wound will be scored with regard to complications and hernia. In addition, a photograph of the perineal wound will be made. A CT-scan will be performed according to the follow-up, and will be assessed for the occurrence of presacral or perineal abscesses and perineal herniation. Quality of Life and urogenital questionnaires will be collected at each follow-up moment (EQ-5D, EORTC-30, EORTC-29, SF36, UDI-6, IIQ-7, IIEF, FSFI, FSDS-R). Additionally, all perineal wound events, re-admissions and re-interventions will be scored.

**Table 1 Tab1:** Southampton wound scoring system

Grade	Appearance
0 – Normal healing	
1 – Normal healing with mild bruising or erythema	A – some bruising
	B – considerable bruising
	C – mild erythema
2 – Erythema plus other signs of inflammation	A – at one point
	B – around sutures
	C – along wound
	D – around wound
3 – Clear or haemoserous discharge	A – at one point only (< 2 cm)
	B – along wound (> 2 cm)
	C – large volume
	D – prolonged (> 3 days)
4 – Pus/purulent discharge	A – at one point only (< 2 cm)
	B – along wound (> 2 cm)
5 – Deep or severe wound infection with or without tissue breakdown	

### Study population

Patients with the following criteria are eligible for inclusion: resection of primary or recurrent rectal cancer by APR, age of 18 years or older, ability to complete follow-up, and written informed consent. Exclusion criteria are total pelvic exenteration or sacral resection above level S4/S5, resection by an intersphincteric APR, biological mesh closure of the pelvic floor, severe systemic diseases affecting wound healing except for diabetes (i.e. renal failure requiring dialysis, liver cirrhosis, and immune compromised status like HIV), collagen disorders (i.e. Marfan syndrome, Ehler-Danlos syndrome) and enrolment in other trials with the same primary endpoint.

### Treatment strategies

In both study arms, APR can start with either the abdominal or the perineal phase. The abdominal phase of the APR can be performed via either laparoscopic or open surgery. The extent of perineal skin excision will be as limited as oncologically justified. The perineal phase of the APR will be performed according to the principles of a complete or limited extralevator APR. This means that the levator muscles will be transected laterally on both sides in order to leave a muscular cuff all around the resection specimen, or that part of the levator muscles will be resected only at the side of the tumour. Routine removal of the coccyx will not take place, unless based on oncological principles or needed to improve surgical visibility. An omentoplasty will not routinely be performed. A transabdominal drain will be placed and removed after 4 days or when the drain production is beneath 100 cc/24 h. The APR specimens will be classified according to Phil Quirke’s classification [6]. Postoperatively, the Enhanced Recovery After Surgery (ERAS) protocol will be followed and the sutures will be removed after 14 days at the outpatient clinic.

#### Perineal closure control arm

Standard practice in the Netherlands and the participating centre in the UK is primary closure of the perineum. This consists of stitching the perineal ischioanal fat together using interrupted 2.0 Vicryl sutures. Afterwards, the subcutaneous fat will be closed using interrupted 2.0 Vicryl sutures. A Redon drain (CH10) will standardly be placed between these layers. Subsequently, the skin will be closed using interrupted Vicryl 3.0 sutures. The perineal redon suction drain will be removed after 14 days or when the production is less than 30 cc/24 h.

#### Perineal closure experimental arm

Perineal closure will be performed or supervised by a surgeon experienced with the gluteal turnover flap. The first gluteal turnover flap procedure at a local participating hospital will always be supervised by an experienced (plastic) surgeon from the study group. When experience with the flap is not sufficiently present after the first time, supervision will be continued as long as required. The patient will be positioned either in prone or lithotomy position as preferred by the operating surgeon. The flap is marked on the gluteal skin on either the right or the left side of the surgical defect with a maximum width of about 2.5 cm. The half-moon shaped skin island is deepithelialised. Subsequently, the flap is developed by incising the dermis and subcutaneous fat with approximately a 45 degree level towards lateral. Gluteal perforators are not selectively dissected, and for this reason there is no need for pre-operative Doppler identification of perforators, which simplifies the procedure. Once developed, the subcutaneous flap is placed into the perineal defect and the deepithelialised dermis is fixed to the contralateral pelvic floor remnant with Vicryl 2.0 sutures. Afterwards, the perineum is closed in layers over the gluteal flap using interrupted 2.0 Vicryl sutures for the subcutaneous fat and Vicryl 3.0 interrupted sutures for the skin. A Redon drain (CH10) will standardly be placed between the flap and the subcutaneous fat and removed after 14 days or when the production is less than 30 cc/24 h. The procedure with accompanying video has been published previously [7].

### Outcome parameters

#### Primary endpoint

The primary endpoint of the study is the percentage of uncomplicated perineal wound healing at 30 days postoperatively. Uncomplicated perineal wound healing is defined as a Southampton wound score of less than two.

#### Secondary endpoints

Secondary endpoints are perineal wound healing according to the Southampton wound grading at 14 days, 3, 6 and 12 months postoperatively; postoperative pain score, the effect of neo-adjuvant treatment on perineal wound healing, incidence of persistent perineal or presacral sinuses both clinically and by imaging (routine follow-up CT), need for re-intervention or re-admission related to perineal wound problems, incidence of symptomatic and asymptomatic perineal hernia during follow-up, length of hospital stay, and quality of life and urogenital function (EQ-5D, EORTC-30, EORTC-29, SF36, UDI-6, IIQ-7, IIEF, FSFI, FSDS-R).

### Sample size calculation

The proportions of patients with uncomplicated perineal wound healing between both study arms will be compared and analysed by the intention-to-treat approach. The hypothesis is that gluteal turnover flap closure increases the uncomplicated perineal wound healing rate compared to primary closure of the perineum.

Our recently conducted pilot study showed promising results of the gluteal turnover flap with a flap failure in zero of ten patients included, and no Clavien-Dindo complications of three or higher within 30 days of surgery. Among the ten patients, there were four minor complications and no major wound complications requiring re-intervention at 30 days postoperatively. The minor complications consisted of two perineal wound dehiscences, one perineal infection necessitating manual drainage and antibiotic therapy, and one non-infected perineal seroma that also required manual drainage. A recent published case series of 13 patients undergoing an APR for rectal cancer with a similar flap procedure showed no cases of flap loss and no donor site or major perineal morbidity [8]. Combining the outcome of our pilot study with the recently published case series results in an uncomplicated wound healing rate of 83% (19/23). In current literature an increase of uncomplicated perineal wound healing of approximately 20% is to be expected when a muscle flap is being used. However, these data are mostly derived from cohort series in which different kinds of flaps were being used, with different definitions of complicated perineal wound healing. Therefore the currently available literature is difficult to interpret with regard to perineal wound healing. In our previously conducted randomised controlled trial (the BIOPEX-study), there was an uncomplicated perineal wound healing percentage of 66% after primary perineal wound closure. Extrapolating the reported improvement in perineal wound healing, a total number of 146 patients (73 per group) are needed to be able to detect a 20% increase in primary perineal wound healing by use of a gluteal turnover flap (from 65 to 85%), applying a Chi-Square test with a two-sided 0.05 significance level and with 80% power. With an estimated drop-out of 10%, a total number of 160 patients are required (80 per group).

### Data analysis

#### Primary endpoint

An intention-to-treat analysis will be performed on the primary outcome using a two-sided Chi-square test to compare the two study groups. A *p-*value of < 0.05 is considered statistically significant. Specific wound complications will be compared between the groups as categorical variables using the Mann-Whitney U test. A Kaplan-Meier survival analysis will be used to analyse the differences in time to perineal wound healing between the two study groups. Statistical analyses will be performed using SPSS software for Windows version 26.

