#### Secondary endpoints

Relative risk with 95% confidence interval will be used to analyse treatment effect according to intention-to-treat. Analysis of binary secondary outcome measures will be performed similar to the primary outcome (such as perineal hernia rate, re-intervention rate, wound complication etc.). All *p*-values will be two-tailed and a p-value of < 0.05 will be considered statistically significant. Subgroup analyses will employ a test of interaction to explore whether there is evidence that the treatment effects differ across subgroups. As with all subgroup analyses these will be interpreted with caution, and will be considered hypothesis generating.

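### The Mann-Whitney U test does not suit unordered wound-complication types, and the sentence does not say which kind of variable is meant

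*Protocol article*

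**What the plan says.** Under Data analysis, Primary endpoint, the article first gives the main test: "An intention-to-treat analysis will be performed on the primary outcome using a two-sided Chi-square test to compare the two study groups". Shortly after, it adds: "Specific wound complications will be compared between the groups as categorical variables using the Mann-Whitney U test".

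The next subsection, Secondary endpoints, gives an effect measure, "Relative risk with 95% confidence interval will be used to analyse treatment effect according to intention-to-treat", and a rule for yes/no outcomes: "Analysis of binary secondary outcome measures will be performed similar to the primary outcome (such as perineal hernia rate, re-intervention rate, wound complication etc".

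The article does not define the specific complications as an analysis variable. The only itemised list is the pilot experience under Sample size calculation: "The minor complications consisted of two perineal wound dehiscences, one perineal infection necessitating manual drainage and antibiotic therapy", followed by one non-infected seroma. An ordered wound outcome does exist and has its own name among the secondary endpoints: "perineal wound healing according to the Southampton wound grading at 14 days, 3, 6 and 12 months postoperatively".

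**The concern.** Mann-Whitney asks whether values in one arm tend to be higher than in the other. For dehiscence, infection and seroma, higher has no meaning until someone assigns codes, and the article gives no order. An unseen analysis plan cannot simply fill this in, because the article does name a test and that test does not match the data type as described.

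The comparison has some interest. The Background argues that filling the dead space should reduce infection and abscess formation, so the pattern of complications bears on the proposed mechanism. Two of the four minor pilot events were dehiscences. A test that responds to coding, or that cannot see a shift from one type to another, would serve that purpose poorly. A rank test also gives no complication rate or relative risk.

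**Working it through.** **1. The plan's own figure.** The only related calculation is the primary sample size, "from 65 to 85%), applying a Chi-Square test with a two-sided 0.05 significance level and with 80% power". With p1 = 0.65, p2 = 0.85 and mean 0.75:

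n per arm = [1.96·√(2·0.75·0.25) + 0.8416·√(0.65·0.35 + 0.85·0.15)]² / 0.20² = (1.2003 + 0.5014)² / 0.04 = 72.4, rounded up to 73.

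This reproduces "a total number of 146 patients (73 per group) are needed", with power 80.3%. It rests on the chi-square test alone, so the Mann-Whitney sentence does not affect it.

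The article gives no complication counts by arm. **All counts below are invented for illustration.** Mann-Whitney p-values are tie-corrected and asymptotic; chi-square is uncorrected Pearson.

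**2. Reading A: one multi-level nominal variable.**

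*Complicated wounds only*, dehiscence/seroma/infection 14/5/6 against 5/12/6. Pearson chi-square = 7.07 on 2 df, p = 0.029. With three categories, only the choice of middle code matters:

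| Category coded in the middle | Mann-Whitney p |
|---|---|
| Infection | 0.009 |
| Seroma | 0.09 |
| Dehiscence | 0.15 |

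*All patients, 73 per arm*, with no complication coded lowest: 47/12/4/10 against 47/4/12/10. Four cells each differ by 4 from an expected 8, so chi-square = 4 × 4²/8 = 8.0 on 3 df, p = 0.046. Mann-Whitney gives 0.51 or 0.77 in every coding, so it misses the shift between types.

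*All patients, 73 per arm, at the design's expected totals.* Complicated wounds are 35% and 15% of 73, about 26 and 11. Split as 47/10/8/8 against 62/5/3/3, with no complication lowest, Mann-Whitney gives 0.004 to 0.006 over all codings and chi-square on 3 df gives 0.041. Coding hardly matters here, because the ranks mainly pick up the difference in any complication: (15/73)² / [(37/146)(109/146)(2/73)] = 8.15 on 1 df, p = 0.004. That says little about which types differ.

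**3. Reading B: each complication yes/no.** Take 28/80 against 12/80.

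- Chi-square = (0.35 − 0.15)² / (0.25·0.75·2/80) = 0.04/0.0046875 = 8.533, p = 0.0035.
- For two categories, the squared tie-corrected Mann-Whitney statistic is chi-square × (N − 1)/N = 8.533 × 159/160 = 8.480, p = 0.0036.

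Reversing the codes changes nothing. The rank test itself gives no effect size; the relative risk is 0.35/0.15 = 2.33.

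**4. Reading C: ordered Southampton grade.** Table 1 runs from 0 (normal healing) to 5 (deep or severe infection). A rank test is appropriate for that scale.

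**The case against.** The strongest reply is that the article never calls the variable nominal. The sentence stands under the primary endpoint, which is built on the Southampton score, and Table 1 places erythema, discharge, pus and deep infection in order. Categorical can include ordered categories, so the authors may already mean Reading C. This possibility stands, and it is why the point is conditional. It does not rescue the wording: the sentence speaks of specific complications, whereas the article calls the ordered outcome Southampton grading.

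A reader might infer that the planned p-value is arbitrary. The document does not support that in general. It holds only under Reading A, and the article describes no single variable merging all types. Such a variable would fit awkwardly anyway, since a patient can have more than one complication. The first two examples were also built with near-equal totals and types swapped between arms, which is the pattern least favourable to a rank test, and the first leaves out uncomplicated patients. At the design's expected totals, coding was immaterial.

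A reader might also infer a flat contradiction between the two Data analysis subsections. That too goes further than the text. The secondary-endpoint rule covers binary outcomes and names wound complication in the singular, which can mean any complication. The other sentence concerns specific complications and may be about different variables. If they are the same yes/no variables, the p-values practically coincide, and the secondary-endpoint subsection already supplies a relative risk.

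**Conclusion.** The point holds in limited form and is minor. As worded, the sentence pairs a rank test with categories for which no order is given, and the only listed examples are unordered. The consequence depends on the reading:

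- **One nominal variable:** the test is unsuitable. It can depend on coding and can miss a shift between types.
- **Yes/no per complication:** there is no material effect on the p-value. The remaining faults are an inconsistent choice of test and no effect estimate from the test named.
- **Southampton grade:** the test is sound and the wording is not.

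The sentence needs rewording under all three. The sizes shown rest on invented counts and illustrate what can happen; they do not predict this trial's result. Comparison of complication types is not listed as a separate secondary endpoint, and the primary test, the 146 evaluable patients and the total of 160 are untouched.

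**What to change.** Replace the Mann-Whitney sentence under Data analysis, Primary endpoint, with wording to this effect: each specific perineal wound complication will be analysed as present or absent per patient, by intention to treat, and reported as a relative risk with 95% confidence interval and a chi-square test, or Fisher's exact test where expected counts are small. The Mann-Whitney U test will be used only for the ordinal Southampton grade.

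This brings the sentence into line with the Secondary endpoints subsection and allows for patients with more than one complication. It costs one sentence in the protocol or analysis plan, with no extra patients or data and no change to power.
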